### Outcome

2.11

#### Primary outcomes

2.11.1

The primary outcomes are DASS-21 total score and PSQI global score. DASS-21 was selected as the primary mental-health outcome, and PSQI was selected as the primary sleep outcome. For both co-primary outcomes, the confirmatory time point of interest will be week 8, with week 4 serving as an intermediate follow-up assessment.

##### Depression, anxiety, and stress scales-21 items (DASS-21)

2.11.1.1

DASS-21 is a 21-item self-report questionnaire that quantifies symptoms of depression, anxiety, and stress. Items are organized into three 7-item subscales and rated from 0 to 3 to reflect symptom severity/frequency. Subscale scores (and an overall total score) are calculated by summing item responses; higher scores indicate greater symptom burden. The instrument has been widely applied in research and community samples and shows acceptable reliability and construct validity (Zhang et al., 2024).

##### Pittsburgh sleep quality index (PSQI)

2.11.1.2

Subjective sleep quality will be assessed with the PSQI, which evaluates overall sleep quality and common sleep disturbances over the previous month. The PSQI contains 19 self-rated items that generate seven component scores (subjective sleep quality, sleep latency, sleep duration, habitual sleep efficiency, sleep disturbances, use of sleep medication, and daytime dysfunction). Each component is scored 0–3 and summed to yield a global score from 0 to 21, with higher scores indicating poorer sleep. A global score >5 is often used to indicate clinically relevant sleep disturbance (Buysse et al., 1989). For this study, the PSQI validated Chinese version will be used.

#### Secondary outcomes

2.11.2

The secondary outcomes provide complementary characterization of POMS total mood disturbance, actigraphy-derived sleep parameters, participants’ strength, body composition, and biological pathways potentially linking resistance training to sleep and mental health. The schedule of enrolment, interventions, and assessments are shown in Table 2.

**Table 2 tab2:** The schedule of enrolment, interventions, and assessments.

Type of research	Data collection component	Content	Baseline (week 0)	Week 4	Week 8
Quantitative research	Eligibility screening and informed consent	Assess criteria; obtain written informed consent; randomize participants (1:1:1)	✓		
	Mental health	DASS-21; POMS	✓	✓	✓
	Sleep outcomes	Wrist-worn accelerometer; PSQI	✓	✓	✓
	Strength	1RM back squat; 1RM conventional deadlift	✓	✓	✓
	Biomarkers	High-sensitivity C-reactive protein; cortisol; serotonin	✓	✓	✓
	Anthropometrics	Weight/height/ body mass index; waist/hip/waist-to-hip ratio; Bioelectrical impedance analysis	✓	✓	✓
	Adherence and safety monitoring	TR/CS: attendance, completion, Adverse events each session; CON: weekly contacts record changes	Continuous/weekly monitoring		

##### Profile of mood states (POMS)

2.11.2.1

The POMS is a self-report inventory designed to capture recent mood states. The 65 adjective items form six domains (tension, depression, anger, vitality, fatigue, and confusion). Participants indicate how strongly each adjective described their feelings over the past week (including the day of assessment) on a 5-point scale from 1 (none) to 5 (extremely). Total mood disturbance is computed by summing the negative domains, subtracting the vitality score, and adding the standard constant; higher values reflect greater overall emotional distress (Schmalbach et al., 2025).

##### Actigraphy-derived sleep parameters

2.11.2.2

Objective sleep will be assessed using wrist-worn actigraphy (e.g., ActiGraph). Sleep parameters will be derived using validated actigraphy algorithms and will include indicators such as total sleep time, sleep efficiency, sleep onset latency, wake after sleep onset, and the number/duration of awakenings (Ancoli-Israel et al., 2015).

##### Maximal dynamic strength

2.11.2.3

Maximal lower-body dynamic strength will be quantified via 1RM testing for the back squat and conventional deadlift, defined as the highest load that can be lifted once through the full range of motion with proper technique. Testing will follow standardized warm-up and incremental loading procedures with adequate rest between attempts; 1RM testing is considered a gold-standard field measure of maximal dynamic strength and demonstrates good-to-excellent test–retest reliability across a wide range of populations and exercises (Grgic et al., 2020). To enhance comparability across repeated measurements, 1RM testing will be performed under the same standardized warm-up, assessor supervision, and pre-test restrictions at each time point (Grgic et al., 2020).

##### Anthropometric measurements and body composition

2.11.2.4

The participants will complete anthropometric assessments barefoot and wearing light clothing. Body mass and height will be recorded using calibrated equipment, and BMI will be calculated as weight (kg) divided by height squared (m^2^). Waist circumference will be measured at the level of the umbilicus and hip circumference at the widest point; each will be taken twice and averaged, and the waist-to-hip ratio will be computed as waist/hip. Body composition will be assessed via bioelectrical impedance analysis using a Tanita TBF-418B device (Tanita Corporation, Tokyo, Japan). Participants will stand on the analyzer with appropriate foot contact on the electrodes; the device applies a low-amplitude alternating current (0.8 mA, 50 kHz) and estimates whole-body and trunk fat mass and percentage fat based on impedance. Reported in-vivo reproducibility for this system is 1.54% (BF), 1.85% (%BF), 2.50% (TF), and 2.79% (%TF) (Zhang et al., 2014). To improve repeatability, body composition assessments will be standardized with respect to time of day, fasting status, bladder voiding, and pre-assessment physical activity.

##### Blood biomarkers

2.11.2.5

To provide an exploratory biological framework for the secondary outcomes, hs-CRP, cortisol, and serotonin were selected *a priori* as peripheral markers representing three biologically plausible pathways through which resistance training may influence mental health and sleep, namely low-grade systemic inflammation, neuroendocrine stress regulation, and serotonergic signaling. Specifically, hs-CRP was included as an index of low-grade systemic inflammation, which may be elevated in sedentary individuals and has been associated with depressive symptoms and sleep disturbance (Pearson et al., 2003; Howren et al., 2009). Cortisol was selected to reflect hypothalamic–pituitary–adrenal axis activity and circadian stress regulation, given its pronounced diurnal rhythm and sensitivity to chronic stress, both of which are relevant to sleep and psychological well-being (Liu, 2024). Serotonin was included as an exploratory peripheral marker related to mood regulation and sleep–wake control, and as a biochemical precursor of melatonin; altered serotonergic activity has been implicated in depression, anxiety, and sleep dysregulation (Monti, 2011; Yohn et al., 2017). Collectively, these biomarkers were intended to provide exploratory insight into inflammatory, neuroendocrine, and serotonergic pathways potentially relevant to intervention-related changes in mental health and sleep, rather than to serve as definitive mechanistic mediators.

Venous blood samples will be collected at baseline, week 4, and week 8 between 07:00 and 09:00 after an overnight fast of at least 8 h. To minimize acute exercise-related perturbations, blood sampling in the TR and CS groups will be scheduled 48–72 h after the most recent training session. Participants will be asked to avoid vigorous physical activity outside the intervention, alcohol, and caffeine for 24 h before sampling. Samples will be collected after a standardized seated rest period and processed according to a pre-specified analyte-specific protocol. After centrifugation, aliquots will be stored at −80 °C until batch analysis. All assays will be performed in the same laboratory by personnel blinded to group allocation, and samples from the same participant will be analyzed within the same assay batch whenever feasible. Intra- and inter-assay coefficients of variation will be recorded and reported.

### Statistical analysis

2.12

All statistical analyses will be performed using SPSS version 26.0 and R software. Except for multiplicity-adjusted analyses of the co-primary outcomes, a two-sided *p*-value of <0.05 will be considered statistically significant. Continuous variables will be summarized as mean ± standard deviation (SD) if approximately normally distributed, or as median (interquartile range) otherwise. Categorical variables will be summarized as counts and percentages. Baseline characteristics will be described by group. The co-primary outcomes will be the DASS-21 total score and the PSQI total score.

The primary analysis will follow the intention-to-treat principle and will use linear mixed-effects models for repeated measures, given the longitudinal design and the possibility of incomplete follow-up (Krueger and Tian, 2004). For each continuous outcome, fixed effects will include group (CON, TR, and CS), time (Baseline, Week 4, and Week 8; treated as a categorical variable), and the group × time interaction, with participant included as a random effect to account for within-subject correlation across repeated assessments. For the co-primary outcomes, the primary inferential tests will focus on the group × time effects, with Holm-Bonferroni correction applied to control multiplicity across the two co-primary outcomes. For each co-primary outcome, the primary contrast will be the between-group difference in change from baseline to Week 8 estimated from the mixed-effects model. Prespecified pairwise comparisons among CON, TR, and CS, including CON versus TR, CON versus CS, and TR versus CS, will be conducted using model-estimated marginal means with adjustment for multiple comparisons. Analyses of Week 4 outcomes and secondary outcomes will be considered exploratory.

Missing outcome data will not be routinely handled by multiple imputation in the primary analysis. Instead, the mixed-model framework will use maximum likelihood estimation based on all available repeated measurements, which provides valid inference under a missing-at-random assumption. To improve transparency, the amount, patterns, and reasons for missing data will be summarized by group and time point (Pugh et al., 2022). If missing data for the primary outcomes are non-negligible, sensitivity analyses using multiple imputation and, where appropriate, an alternative missing-data framework (eg, pattern-mixture analysis) will be performed to assess the robustness of the findings to departures from the primary assumption.

Model assumptions will be examined using residual diagnostics. Variables with marked skewness, particularly biomarker measures, may be transformed as appropriate before modelling. Results will be reported as model-based estimated mean differences or regression coefficients with 95% confidence intervals. Standardized effect sizes will also be presented for key between-group contrasts where appropriate.

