### Participants

2.2

Participants will be sedentary female college students from universities in Beijing. They will be randomly assigned in a 1:1:1 ratio to CON, TR, or CS. We plan to enroll 48 participants (16 per group). The inclusion and exclusion criteria are as follows.

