### Sample size estimation

2.3

Although the final efficacy analyses will use linear mixed-effects models, sample size was estimated at the design stage using the repeated-measures ANOVA interaction framework in G*Power as a pragmatic approximation for a three-group repeated-assessment trial. The primary outcomes for sample size calculations are DASS-21 scores and PSQI scores. Two-sided tests with effect size *f* = 0.25, *α* = 0.05, and power (1-*β*) = 80% were used with three groups and three measurements. The minimum total sample size required for the study was determined to be 36 participants after sample size calculation with repeated measures analysis of variance (between-group-within-group interaction) using G * Power Software (version 3.1.9.7) (Kang, 2021). Considering a potential dropout rate of 20–25% based on our previous similar studies, we decided to recruit 48 eligible young women.

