### Randomization and blinding

2.5

After completion of baseline assessments and confirmation of eligibility, participants will be randomly allocated in a 1:1:1 ratio to the non-exercising control group (CON), traditional resistance training group (TR), or rest-redistribution cluster-set resistance training group (CS). The allocation sequence will be generated by an independent researcher who is not involved in participant recruitment, intervention delivery, outcome assessment, or statistical analysis, using a computer-generated permuted-block randomization scheme with variable block sizes. Variable block randomization was selected because the planned sample size is modest and approximate balance across the three groups should be maintained throughout enrolment, while undisclosed variable block sizes reduce the predictability of allocation. Stratification by baseline DASS-21 or PSQI score will not be used, because simultaneous stratification by multiple symptom measures in a small three-arm trial may create sparse strata and increase operational complexity without a clear gain in allocation efficiency. To ensure allocation concealment, group assignments will be placed in sequentially numbered, opaque, sealed envelopes and stored securely by the independent researcher. Study staff responsible for enrolment will confirm eligibility and complete baseline assessments before opening the next envelope in sequence, and these staff will have no prior access to the allocation sequence.

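### The primary model leaves baseline free in each arm, so the week-8 contrast is an unadjusted change score: valid, but exposed to chance baseline imbalance and less precise than a baseline-adjusted analysis

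*Protocol article*

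**What the plan says.** The Statistical analysis section (2.12) gives the fixed effects as group, "time (Baseline, Week 4, and Week 8; treated as a categorical variable), and the group × time interaction". Dependence between a woman's repeated scores is left to a random effect for participant, read here as a random intercept. For each co-primary outcome, DASS-21 total and PSQI global score, "the primary contrast will be the between-group difference in change from baseline to Week 8 estimated from the mixed-effects model". Section 2.12 names neither a baseline covariate nor a common baseline mean across arms.

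Randomization and blinding (2.5) states that "Stratification by baseline DASS-21 or PSQI score will not be used", and gives sparse strata in a small three-arm trial as the reason.

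Both co-primary scores are also entry criteria (2.2.1): DASS-21 of at least 44 and PSQI of at least 7. Table 2 lists eligibility screening and these questionnaires in the same baseline column. Recruitment (2.4) mentions a screening visit and, later, completed baseline assessments. It does not say whether the two scales are measured again between them.

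**The concern.** With a group main effect and a full interaction, the model estimates nine separate cell means (three arms by three times). The week-8 contrast then subtracts each arm's own baseline mean in full, which amounts to assuming a slope of 1 for week 8 on baseline. Repeated symptom scores normally have a slope below 1. An arm that happens to start higher will then appear to improve more, for reasons unrelated to training.

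The planned arms have 16 participants, so such imbalance is not rare, and the design does not limit it. Imbalance would feed into both co-primary results and into all three pairwise comparisons. A trial with little precision to spare would also leave baseline information unused.

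**Working it through.** **Inputs.** From the article: 16 per arm (2.2), effect size f = 0.25, alpha 0.05, 80% power, three groups, three measurements (2.3). Assumed, because the article does not give it: the baseline to week-8 correlation ρ, taken as 0.3 to 0.7. Differences are in SD units.

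**1. The plan's own figure.** "The minimum total sample size required for the study was determined to be 36 participants". With λ = f²·N·m/(1 - ρ) and ρ = 0.5, N = 36 gives λ = 0.0625 × 36 × 3 / 0.5 = 13.5 on 4 and 66 df, and power 0.823. N = 33 gives 0.781. So 36 is the smallest equal-arm total, and 36/0.75 = 48 matches the recruitment target. The figure reproduces at ρ = 0.5, which is an inference and not a stated input.

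**2. What the written model estimates.** On simulated complete data its week-8 interaction coefficient was -0.5568. The raw difference in mean change was also -0.5568. With missing visits the two are no longer identical, but baseline remains free by arm.

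**3. Chance imbalance.** The SD of a baseline difference between two arms is √(2/16) = 0.354, and √(2/12) = 0.408 after 25% dropout. The chance that it exceeds 0.5 SD in either direction is 16% and 22%. Given an imbalance d, the change-score contrast shifts by -(1 - slope)·d. At slope 0.5 and d = 0.5 the shift is -0.25 SD. Simulated shifts per unit of imbalance were -0.71, -0.50 and -0.32 at ρ = 0.3, 0.5 and 0.7, and about 0 for the adjusted estimate.

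**4. Precision, baseline not truncated.** The variance of the contrast is 2(1 - ρ)·2/n for change and (1 - ρ²)·2/n after adjustment, so the ratio is (1 + ρ)/2. Estimating the slope multiplies the adjusted variance by 1 + 1/(N - 5): 1.023 at N = 48 and 1.032 at N = 36. At 16 per arm, two-sided 0.05, 80% power, one pair:

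| ρ | Ratio | Ratio with slope cost | Detectable difference, change | Detectable difference, adjusted |
|---|---|---|---|---|
| 0.3 | 0.65 | 0.67 | 1.20 | 0.98 |
| 0.5 | 0.75 | 0.77 | 1.01 | 0.89 |
| 0.7 | 0.85 | 0.87 | 0.78 | 0.73 |

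**5. Precision, screening score used as baseline.** An entry cut-off shrinks the baseline SD relative to week 8. If s is that SD ratio and r the correlation among those enrolled, the variances are proportional to s² + 1 - 2rs (change) and 1 - r² (adjusted). Take ρ = 0.5 with a cut-off 0.5 SD above the population mean, which gave s = 0.58 and r = 0.29. Change: 0.336 + 1 - 0.336 = 1.00. Adjusted: 1 - 0.084 = 0.916, or 0.937 with the slope cost; simulation gave 0.941. Over the correlations and cut-offs tried, the ratio was about 0.87-1.00. A separate simulation with milder cut-offs gave 0.84-0.97. The imbalance shrinks too: with s of 0.54-0.73 it is 0.354 × s = 0.19-0.26 week-8 SD, and the shift at slope 0.5 is 0.10-0.13.

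**6. Choice of adjusted model.** With no treatment effect, 16 per arm, nominal 5% and a truncated baseline, a shared baseline mean combined with only a participant random intercept rejected in about 7.5-10.6% of runs. The baseline-covariate model rejected in 4-5.5%, and the written model in 4.1-4.7%. The random intercept imposes equal variances at all visits. At ρ = 0.5 with a cut-off at +1 SD, the constrained model reported a standard error of 0.260 against an empirical 0.312.

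**The case against.** The strongest reply is that nothing here is an error. A mixed model with free baseline means is standard, it targets the contrast that the article names, and randomization makes it unbiased on average. That stands. A reader might infer that the primary result will be biased or the test invalid. The article does not support this, because the shift exists only conditionally on a realised imbalance, and the written test holds its level.

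A second reply is that the gain may be small. That also stands. A reader might take the ratio of 0.75 at ρ = 0.5 as the saving, equivalent to 1/0.75 = 1.33 times the participants. That needs an unstated correlation and an untruncated baseline, whereas both outcomes are used to select participants. Selection on high scores is also not a reason for a lower slope: under a linear relation it leaves the slope unchanged and shrinks the baseline variance, which reduces the benefit.

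A third reply is that covariates can be left to a statistical analysis plan. This is weaker, because section 2.12 already fixes the model and the primary contrast. The reason given for not stratifying is sound, but it makes adjustment in the analysis more useful, not less.

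**Conclusion.** The point holds as an improvement in efficiency and conditional accuracy, not as a flaw that invalidates the analysis. The written contrast is an unadjusted difference in change. For ρ of 0.3-0.7, baseline adjustment brings its variance to about 0.65-0.85 of the planned value if baseline is untruncated and separate from screening, and to about 0.87-1.00 if the truncated screening score is used. In both cases it removes the dependence on chance imbalance. These ranges rest on assumed correlations, roughly normal scores and a linear relation with baseline.

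A reader might also infer that any form of baseline adjustment will do. It will not: a common baseline mean added to the random-intercept model of section 2.12 can roughly double the type I error when entry cut-offs truncate the baseline.

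**What to change.** In section 2.12, for both co-primary outcomes, model the week-4 and week-8 scores with group, time, group × time, baseline score and baseline × time, keeping the participant random effect. Report the adjusted week-8 mean difference between arms as the primary estimate; with baseline as a covariate this equals the adjusted difference in change.

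Reword the sentence on the primary inferential tests to refer to the week-8 group contrasts. Once baseline is no longer a level of time, group × time only tests whether the effect differs between weeks 4 and 8. The Holm step across the two outcomes is unaffected.

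If a shared-baseline longitudinal model is preferred, specify an unstructured covariance and not a random intercept alone. State also whether the screening questionnaires serve as the baseline values.

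The cost is about one parameter per time point, some 2-3% of variance, and no extra data. Participants with no follow-up score drop out of the covariate model, so they should be counted in the missing-data summary. The change should be fixed before group labels are unmasked, since adjusting after seeing an imbalance would be post hoc.

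### A participant random intercept fitted by maximum likelihood makes the week-8 standard error 3–4% too small at 12–16 per arm, and by more if correlation falls with time between visits

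*Protocol article*

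**What the plan says.** All of this is in the protocol article. Section 2.12 (Statistical analysis) specifies a linear mixed model with group, "time (Baseline, Week 4, and Week 8; treated as a categorical variable"), and their interaction, "with participant included as a random effect to account for within-subject correlation across repeated assessments". It names no random slope, residual covariance structure or robust standard error. The confirmatory quantity is fixed in the same section: "the primary contrast will be the between-group difference in change from baseline to Week 8 estimated from the mixed-effects model". The paragraph on missing data adds that "the mixed-model framework will use maximum likelihood estimation based on all available repeated measurements".

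On size, section 2.2 (Participants) sets enrolment at 48, or 16 per group. In section 2.3 (Sample size estimation), "The minimum total sample size required for the study was determined to be 36 participants", which is 12 per group. No between-visit correlation or standard deviation is given anywhere.

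**The concern.** With a single random intercept, every pair of visits is taken to be equally correlated and every visit equally variable (compound symmetry). The standard error of the baseline-to-week-8 change is then built from a within-participant variance averaged over all three pairs of visits. The confirmatory contrast uses only one pair, the one furthest apart. If that pair is less correlated than the others, the averaged variance is too small for it.

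Separately, ML divides the within-participant sum of squares by a count that ignores the estimated fixed effects, whereas REML subtracts them. At 12–16 per arm the difference is visible.

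At stake are the p-values and confidence intervals of the confirmatory comparison. The Holm step across the two outcomes and the adjustment of the pairwise comparisons both take the model's p-values as given, so neither repairs a standard error that is wrong to begin with.

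**Working it through.** **Inputs from the protocol.** Three groups, three visits, N = 36 (minimum) or 48 (enrolled), 12 or 16 per arm, two-sided 5%.

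**The plan's own sample size.** With f = 0.25, three groups and three measurements, and assuming a correlation of 0.5 and sphericity (neither is stated), the noncentrality at N = 36 is 0.25² × 36 × 3 / (1 − 0.5) = 13.5 on 4 and 66 degrees of freedom. Power is 0.823; at N = 33 it is 0.781. So 36 reproduces, and 36 / (1 − 0.25) = 48 reproduces the enrolment target. That calculation is not in dispute.

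**Effect of ML.** With complete balanced data the within-participant sum of squares is divided by 2N under ML and by 2(N − 3) under REML. The ratio of standard errors is √((N − 3)/N):
- N = 36: √(33/36) = 0.957, or 4.3% too small.
- N = 48: √(45/48) = 0.968, or 3.2% too small.

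**Effect of the random intercept.** Let r̄ be the mean of the three pairwise correlations and r₀₈ the baseline–week 8 correlation. With equal variances, the ratio of the model standard error (REML) to the true one is √((1 − r̄)/(1 − r₀₈)). N does not appear in it. The correlations below are assumptions, in the order baseline–week 4, week 4–week 8, baseline–week 8:
- 0.6/0.6/0.4: r̄ = 0.533; √(0.467/0.600) = 0.882.
- 0.7/0.7/0.49: r̄ = 0.630; √(0.370/0.510) = 0.852.
- 0.5/0.5/0.6 (no decay, longest gap most correlated): r̄ = 0.533; √(0.467/0.400) = 1.080.

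Multiplying by the ML factor at N = 36 gives 0.844, 0.816 and 1.034. At N = 48 it gives 0.854, 0.825 and 1.046.

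**Type I error by simulation.** One unadjusted pairwise week-8 contrast, nominal 5%, complete data, t reference, 20,000 or 40,000 trials per scenario (simulation error about 0.2 points at a rate of 10%):

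| Assumed correlations | Intercept + REML, 12/arm | Intercept + ML, 12/arm | Intercept + ML, 16/arm |
|---|---|---|---|
| Equal (0.5 or 0.7) | 5.1–5.3% | 6.1–6.3% | 5.6–5.8% |
| 0.6/0.6/0.5 | 6.6% | 7.8% | 7.6% |
| 0.6/0.6/0.4 | 8.4% | 9.7% | 9.6% |
| 0.7/0.7/0.49 | 9.6% | 11.0% | 10.3% |
| 0.5/0.5/0.6 | 3.5% | 4.2% | 3.9% |

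Estimating the variance of the baseline-to-week-8 change directly, as an unstructured covariance with REML does for complete data, gave about 5% in these settings.

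**Entry cut-offs.** Selecting participants on a high baseline score was simulated with the cut-off 0 to 1 SD above the mean and equal correlations of 0.5–0.7 before selection (all assumed). Random intercept plus ML then gave 0.97–1.00 of the true standard error and error rates of 4.8–5.8%.

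**The case against.** The strongest reply is that the article does not fix the model as tightly as this reading assumes. It never uses the words intercept or compound symmetry, and covariance structure and degrees-of-freedom method are details that a condensed article may leave to a fuller plan. Maximum likelihood appears only in the missing-data paragraph, where it is contrasted with multiple imputation, so it may be a generic term that includes REML. The article also promises residual diagnostics. This stands as a reason for caution: the point rests on the plain reading of the text. It does not remove the point, because the participant effect is the stated device for within-subject correlation and maximum likelihood is the stated method. If something else is meant, the wording needs correcting.

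The second reply is that the larger figures depend on correlations the protocol does not give. That stands in full.

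Three stronger readings are tempting and are not supported:
- A reader might infer that the model necessarily understates the standard error by 12–20%. It does so only under decay; with the longest gap most correlated, the standard error is too large.
- A reader might infer that the entry thresholds (DASS-21 ≥ 44, PSQI ≥ 7) make matters worse by truncating the baseline. The check above shows no added harm from truncation.
- A reader might blame the small sample for the whole problem. Only the ML part depends on the number per arm; more participants would not cure the random-intercept part, nor would changing to REML alone.

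Finally, the rates are for one unadjusted contrast, so they are not the trial's overall error rate.

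**Conclusion.** The point holds in two parts of different strength.

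The ML part follows from the text as written: with complete data, the standard error is 3–4% smaller than under REML and type I error is about 6% instead of 5%, even if compound symmetry is exactly right. It is small.

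The random-intercept part can be larger but is conditional. Under the decaying correlations assumed here, intercept plus ML gives a standard error about 15–18% too small and an error rate of about 10–11%; milder decay gives just under 8%. With equal correlations only the ML part remains, and with the reverse pattern the test is slightly conservative. Nothing in the protocol says which case applies, so no single inflation figure can be claimed for this trial. A change is still worth making, because the confirmatory contrast need not depend on an assumption that three visits make unnecessary.

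**What to change.** In section 2.12, for both co-primary outcomes:
- replace the participant random effect with an unstructured 3 × 3 within-participant covariance over baseline, week 4 and week 8;
- replace maximum likelihood with REML, keeping the statement that all available measurements are used;
- name Kenward-Roger (or Satterthwaite) degrees of freedom;
- prespecify one simpler covariance structure, to be used only if the unstructured model does not converge.

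REML without the covariance change would remove only the 3–4% part. The cost is a change of wording, six covariance parameters instead of two, and possibly slightly wider intervals. No extra data or participants are needed to make the change.
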